| **Statistical considerations**  **Design**: phase II  **Nr of patients**: based on results obtained with chemotherapy a progression free survival of >= 60% could be expected at 3 months. The treatment will be considered for further development if a PFS > 70% can be obtained at 3 months. The treatment will be considered inappropriate as a first line if PFS < 50% at 3 months. Therefore a maximum of 40 patients will be included plus the number needed to replace patients that will drop out for reasons other than disease progression and patients not meeting eligibility criteria. |

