# Statistical considerations

The purpose of this study is to obtain an estimate of the proportion of patients experiencing a progression free survival (PFS) at three months in order to position this type of first-line therapy for further study in comparison to the results that can be obtained with current first-line chemotherapy in advanced non-small cell lung cancer.

The premises for the sample size determination are as follows:

With current chemotherapy, progression free survival of 60% or less is obtained at 3 months follow-up3.

Taking into account the general better tolerability of RTKI’s it is proposed that if a PFS of > 70% can be obtained, that this treatment definitely deserves further evaluation against chemotherapy in the first-line treatment of advanced non-small cell lung cancer.

If the study results in a PFS less than 50 % at three months, single agent RTKI’s should not be further evaluated in this setting as outcomes inferior in terms of efficacy to the current standard are not acceptable.

Based on these premises, a one step Fleming design requires at least 33 patients to be included in the study (

With the provision of a margin for eligibility/evaluation issues, the prospective number of patients to be included will be 40 patients.

When, alternatively, statistics normally used for phase II design based on response, are applied to the PFS outcome proportions (freedom from progression regarded as a clinical benefit response), then, in a Simon minimax two-stage design and with α = 5%, β = 20%, for rejecting the null hypothesis (p0) of a freedom from progression rate < 60%, in a first stage, more than 8/13 patients should have a progression free survival of > 3 months. The second stage would lead to an accrual of 35 evaluable patients of whom at least 26 should be free from progression at 3 months to establish a probable freedom from progression rate of > 80% at 3 months. Again, with the provision of a margin for eligibility/evaluation issues, the prospective number of patients to be included will be 40 patients.

With an estimated maximal 10% mutation rate in the overall population of NSCLC, this cohort of patients could result from a baseline population of at least 400 patients with advanced non-small cell lung cancer.

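### The Simon two-stage figures reproduce, but 26 or more of 35 rejects a 3-month rate of 60% or less; it does not establish a probable rate above 80%

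*Protocol*

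**What the plan says.** Statistical considerations first gives a one-step Fleming calculation built on 3-month thresholds of more than 70% and less than 50%. It then offers a second calculation, introduced as an alternative, "in a Simon minimax two-stage design and with α = 5%, β = 20" percent. Its terms are:

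- the null, "for rejecting the null hypothesis (p0) of a freedom from progression rate < 60" percent;
- the first stage: "in a first stage, more than 8/13 patients should have a progression free survival of > 3 months";
- the final rule: "accrual of 35 evaluable patients of whom at least 26 should be free from progression at 3 months";
- what meeting the final rule is for: "to establish a probable freedom from progression rate of > 80% at 3 months".

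The section does not label 80% as the design alternative or as the rate at which power is 80%. The figure appears only as what a positive result shows. Both calculations end at the same planned total: "the prospective number of patients to be included will be 40 patients".

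The Protocol synopsis does not mention the Simon design, the 26/35 cutoff or 80%. Its criterion for going on is: "The treatment will be considered for further development if a PFS > 70% can be obtained at 3 months".

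**The concern.** A Simon design tests one null rate. Crossing the final cutoff rejects that null, here 60% or less. The second rate only fixes the power. The sentence turns it into the conclusion of a positive trial, although the cutoff, 26/35, is an observed proportion below 80%.

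What is at stake is how a pass just at the cutoff gets described. The section sets the result against chemotherapy, taken as 60% or less at 3 months. An observed 74% is about 14 points above that benchmark. Described as a rate probably above 80%, the same result becomes a gain of more than 20 points.

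**Working it through.** **Inputs**, all from Statistical considerations: null rate p0 = 0.60; alpha 0.05; beta 0.20; stage 1 n1 = 13, continue if at least 9 are progression-free; final n = 35, success if at least 26. Taking p1 = 0.80 as the alternative is an inference from the sentence, and step 1 tests it. Alpha is taken as one-sided, as is usual for a Simon design; the protocol does not say.

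**Step 1. Reproduce the stated design.** With X1 ~ Bin(13, p) and X2 ~ Bin(22, p),

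P(pass | p) = sum over x = 9 to 13 of P(X1 = x) × P(X2 ≥ 26 − x).

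| x | term at p = 0.60 | term at p = 0.80 |
|---|---|---|
| 9 | 0.1845 × 0.0722 = 0.0133 | 0.1535 × 0.7326 = 0.1125 |
| 10 | 0.1107 × 0.1584 = 0.0175 | 0.2457 × 0.8670 = 0.2130 |
| 11 | 0.0453 × 0.2898 = 0.0131 | 0.2680 × 0.9439 = 0.2530 |
| 12 | 0.0113 × 0.4540 = 0.0051 | 0.1787 × 0.9799 = 0.1751 |
| 13 | 0.0013 × 0.6244 = 0.0008 | 0.0550 × 0.9939 = 0.0546 |
| Sum | 0.0499 | 0.808 |

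(Sums are from unrounded terms.) A search for the smallest n with type I error at most 0.05 at 0.60 and power at least 0.80 at 0.80, then the smallest expected n under 0.60, returns exactly 8/13 and 25/35, that is, success at 26 or more. The stated figures are therefore right, and 80% is the design's alternative.

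**Step 2. How often does the rule pass when the true rate is below 80%?** The same formula gives:

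| True 3-month rate | P(pass) |
|---|---|
| 60% | 0.050 |
| 70% | 0.327 |
| 75% | 0.575 |
| 79% | 0.768 |
| 80% | 0.808 |

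The rule hardly separates rates just below 80% from rates at 80%.

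**Step 3. What does the cutoff result show?** 26/35 = 74.3%. The Clopper-Pearson 95% interval is 56.7% to 87.5%, and the one-sided 95% lower limit is 59.4%; both ignore the two-stage design. If the true rate were exactly 80%, a single-stage sample of 35 would give 26 or more with probability 0.854, so reaching 26 is no evidence of a rate above 80%.

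**Step 4. Does the word 'probable' rescue the sentence?** Assume a uniform prior. After k of 35 the posterior is Beta(1 + k, 36 − k), whatever the stopping rule. P(rate > 80%) is:

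| k | k/35 | P(rate > 80%) |
|---|---|---|
| 26 | 74.3% | 0.17 |
| 27 | 77.1% | 0.28 |
| 28 | 80.0% | 0.43 |
| 29 | 82.9% | 0.60 |

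With a Jeffreys prior the value at 26 is 0.20. For comparison, rejecting a rate of 80% or less at one-sided 5% in a single stage needs 33/35 (tail 0.019; 32/35 gives 0.061).

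**Step 5. Does the 5% depend on stage 1?** Yes. If 26 of 35 is applied without the stage 1 stop, P(X ≥ 26 | n = 35, p = 0.60) = 0.0575.

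**The case against.** Three objections carry weight.

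*A pass as an event does favour high rates.* The protocol speaks of at least 26, not exactly 26. Under the same uniform prior, P(rate > 80% | pass) is the integral of P(pass | p) over p from 0.8 to 1, divided by the integral over 0 to 1, which is 0.72. A reader might infer from the cutoff result that passing says nothing about exceeding 80%. That goes too far, since averaged over all passing results the word 'probable' can be defended. It still fails count by count: the trial will report a count, and at 26, 27 or 28 a rate above 80% is less likely than not.

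*The Simon calculation may not govern the conclusion.* It is introduced as an alternative and is worded conditionally. The section's stated purpose is to estimate the 3-month proportion, and the thresholds given in both the synopsis and the statistical section are above 70% and below 50%. A reader might infer that the trial's primary conclusion will be wrong. The protocol does not support that: nowhere does it commit the report to claiming more than 80%, and an observed 74.3% already meets the above-70% criterion.

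*Nothing operational changes.* This stands in full: 13, 35, 26 and the 40 planned patients are all unaffected.

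It could also be said that 80% is loose shorthand for the alternative. That is probably its origin, but the sentence presents it as what the result establishes, and the section nowhere calls it the alternative.

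**Conclusion.** The inference in the sentence is wrong; the design figures are right. Meeting both stages rejects a 3-month rate of 60% or less at type I error 0.0499, with power 0.808 if the true rate is 80%. It does not establish a rate above 80%: the cutoff is 74.3%, and a pass occurs about one time in three at a true rate of 70% and more than half the time at 75%.

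The pass probabilities are exact binomial and assume 35 evaluable patients and an enforced stage 1 stop. The posterior figures rest on an assumed uniform prior.

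One further reading should be avoided: that 26/35 taken alone just excludes 60%. Its one-sided 95% lower limit is 59.4%, so it does not. The rejection comes from the two-stage rule.

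Severity is moderate to minor: an error of stated interpretation, with no effect on sample size or cutoffs.

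**What to change.** Replace the closing clause of the Simon sentence with wording such as: *after more than 8/13 in stage 1, 26 or more of 35 rejects a 3-month rate of 60% or less (one-sided alpha 5%; power about 81% if the true rate is 80%).* Drop the claim that a pass establishes a rate above 80%. Add a note that the 5% holds only if the stage 1 stop is applied, because 26 of 35 without it has a type I error of 5.8%.

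This changes one sentence and adds a note. It adds no patients, visits or data and leaves both cutoffs and the planned 40 as they are. The only cost is a less favourable stated conclusion.

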# Translational aspect

## Mutation analysis

Paraffin embedded and formalin fixed tissue will be collected at diagnosis with an informed consent before inclusion in the trial. If possible frozen tissues will also be collected.

Preferably percutaneous biopsies of primary and/or metastatic disease sites will be obtained. Endobronchial biopsies can also be considered for mutations analysis but the success rate might be less. If the patient was treated for locoregional disease, biopsy material from that treatment episode is also suitable for mutation analysis. Surgical specimens will increase the mutation detection rate significantly.

**Recommended fixation method:**

Solution: Neutral buffered 4% Formaldehyde

100ml 40% formal in 900ml distilled H2O and 4g NaH2PO4 - H2O + 6,5g Na2HPO4

Fixation duration: < 24 hrs, **preferably 6-8h**. For small endobronchial biopsies 2hrs is sufficient.

The presence of EGFR mutations in the tumour DNA will be determined or at least confirmed if initially determined elsewhere, in the Laboratory of Molecular Oncology ([name]) of the Department of Medical Oncology-VUB. To maximally increase the mutation rate in the samples considered for mutation analysis, the patients will be preselected on the basis of their phenotype: adenocarcinoma in never-smokers or former smokers who quit smoking > 1 year before inclusion and with less than 15 pack years of smoking.

A tissue slice with a volume of 2 mm3 can reliably be analysed. In a significant proportion the kinase domain mutations can also be determined in very small amount of tissues, but then the chance of finding a mutation decreases. In samples containing less than 50% tumour samples, tissue macro/microdissection will be used to enrich for malignant cells.

Other participating centres can, if they wish, have the samples analysed in their own laboratories and, upon finding a mutation, include the patient in the study. Later the mutation needs to be confirmed in the central lab in order to have a standardized inclusion criterium.

The results of the mutational analysis will be available within 2 weeks, after which the patient can be included in the study.

The presence of mutations will be screened for by DGGE method on exons 18 through 21 and sequencing analysis of exon 19 and 21. The exons examined will be those in which previously mutations have been found (9, 10). This analysis might be extended when additional mutation data become available.

The result needed for inclusion in the study will be based on the highly reliable DGGE methodology and will be delivered within 2 weeks of arrival of the sample at the laboratory.

All mutations will be confirmed by automatic sequencing. In case of (unlikely) non-confirmation of the DGGE result by the subsequent mutation analysis, the patients can continue with the treatment if the clinician judges this to be in the interest of the patient. However such patients will not be included in the final efficacy analysis and will therefore be replaced.

## Additional biomarkers

Determination of additional biomarkers will be assessed if other scientific evidence indicating their potential relevance with regard to the EGFR inhibition becomes available.

Such additional biomarkers including the amount of EGFR/pEGFR, HER2/neu receptor, Erk/pErk will be studied in the laboratory of experimental pathology (EXPA), VUB and other participating labs with specific expertise.

# Documentation and use of study data

## Documentation of study data

A case report form (CRF) will be provided for every patient as a computerized data base record (PDF).

A hard copy of the CRF will be generated by printing the completed pages of the computerized CRF.

The participating investigator, or designated representative, should complete the CRF as soon as possible after the information is collected. The completed CRF must be reviewed and signed by the investigator named in the clinical study protocol or by a designated sub-investigator.

## Intellectual property, authors rights and publications

This is an investigator initiated trial. Its scientific data are the property of all the investigators and of its study coordinators more specifically. No data can be released at any occasion without the prior approval of each of its study coordinators. The following rules guide the authorship of its manuscripts:

All manuscripts and abstracts dealing with the results of the phase II study will mention the names of all the study coordinators and those investigators who contributed at least 10% of evaluable patients. Those institutions contributing 20% or more of the evaluable patients can access to a second authorship. The sequence of the authorship will be according to the respective accrual of the participating institution, the first and corresponding author being the principal investigator and the last author one of the study coordinators.

If separate manuscripts on technical aspects of the mutational analysis or PET scan results would be submitted, it will contain the names of the study coordinators and of all the investigators involved in those technical aspects, according to the respective contribution to the success of the study. Here, the first author will be the investigator who has actually written the manuscript and the last and corresponding author the principal investigator of the overall study.

The principal investigator has final responsibility in applying these provisions and in writing up the main study result.

# Ethical and legal aspects

## Good clinical practice (GCP)

This study is to be conducted according to the globally accepted standards of good clinical practice (as defined in the ICH E6 Guideline for Good Clinical Practice, 1 May 1996), in agreement with the latest revision of the declaration of Helsinki and in keeping with local regulations.

## Patient study-files

Individual patient-study files (clinical report files, CRF) will be established in parallel to the hospital patient file. The CRF-file will exist as a computer-file (in MS Access) and a hard copy. The hard copy will be retained at the data management office at the treating medical center. A hard copy will be retained for at least 15 years after the completion of the study.

## Patient Informed Consent

Prior to the screening evaluation, the patient will be informed of the nature of the study drugs and procedures and will be given pertinent information as to the intended purpose, possible benefits, and possible adverse experiences. The procedures and possible hazards to which the patient will be exposed will be explained. Two approved informed consent statements, one for the mutation analysis and one for the treatment phase will then be read and signed by the patient, and, when required, a witness, and the investigator. The patient will be provided with a copy of the signed informed consent statements. The patient may withdraw from the study at anytime without prejudicing future medical treatment. Verification of the signed informed consent statements will be noted on the patient's study case report form.

## Ethical Committee/Institutional Review Board

The final approved protocol and the informed consent statements will be reviewed by a properly constituted Ethics Committee/IRB. The Ethics Committee's/Board's decision concerning the conduct of the study will be made in writing to the investigator.

The investigator will make required progress reports to the Ethics committee/IRB, as well as report any treatment related deaths.

The investigator will inform the Ethics Committee/IRB by of the termination of the study.

## Ethical Considerations

Eligible patients will be asked if they wish to participate in the study. The outline of the study will be explained by one of the staff physicians. In case the patient refuses to participate this will be respected and "standard" treatment will be offered.

## Insurance

The insurance has been taken by the sponsor (AZ-VUB) with regard to this study protocol, in order to cover all participating investigators, co-investigators and staff involved in this academic, non-commercial trial.

## Modification of the protocol

Any modifications to the protocol which may impact on the conduct of the study, potential benefit of the study, or may affect patient safety, including changes of study objectives, study design, patient population, sample sizes, study procedures, or significant administrative aspects will be made by a formal amendment to the protocol. The Ethics Committee/IRB will approve such amendment prior to implementation.

# Study monitoring

The central datamagement of the study will collect the date from the clinical report files at regular intervals after contacting the collaborating investigators. The availability of a computerized CRF will facilitate the data transfer by email or post.

In case of on site monitoring of source documents, the participating investigators must ensure direct access to the on-site study documentation and medical records.

# Appendices

1. Serious adverse event (SAE) report fill out form.
2. Patient’s information sheets and informed consent.
3. WHO scale for performance status and correspondence with Karnofsky index
4. Common Terminology Criteria for Adverse Events v3.0 (CTCAE) Publish Date: June 10, 2003. Will be provided as a PDF file on CD-ROM.
5. CT and FDG scan specifications.

Concomitant medication list excluding participation (CYP 3A4 inhibitors-inducers)

# 19 Appendix 1 SAE reporting form

# 19 Appendix 3 WHO - KPS

| WHO-SCALE [Grade] | | KARNOFSKY-SCALE [%] | |
| --- | --- | --- | --- |
| 0 | Able to carry out all normal activity without restriction. | 100 | Normal, no complaints |
| 1 | Restricted in physically strenuous  activity by ambulatory and able to carry out light work. | 90 | Able to carry on normal activities; minor signs or symptoms of disease |
| 80 | Normal activity with effort. |
| 2 | Ambulatory and capable of all  self-care but unable to carry out  any work; up and about more than 50 % of waking hours. | 70 | Cares for self. Able to carry on normal activity or to do active work. |
| 60 | Ambulatory. Requires some assistance in activities of daily living and self-care. |
| 3 | Capable of only limited self-care;  confined to bed or chair more than 50 % of waking hours. | 50 | Requires considerable assistance of frequent medical care. |
| 40 | Disabled; requires special care and assistance. |
| 4 | Completely disabled; cannot carry on any self-care: totally confined to bed or chair. | 30 | Severely disabled; hospitalization indicated though death not imminent. |
|  |  | 20 | Very sick; hospitalization and active supportive treatment. |
|  |  | 10 | Moribund. |
|  |  | 0 | Dead. |

# 19 Appendix 4 CTC AE 3.0

# 19 Appendix 5 Imaging Specifications

All CT-scan performed within this study will be spiral CT-scans.

### PET-scan for evaluation of metabolic response

Patient preparation

- 6 hours fasting (postpone patient if not fasted)
- valium p.o. prophylaxis if needed
- diabetes patients under peroral treatment: overnight fasting; no peroral antidiabetics in the morning; plan patient early in morning; if glycemia > 140 and < 200 mg%  follow scheme here under.
- in insuline-dependent diabetes patients: plan patient early in the morning after overnight fasting; no insuline in the morning.

-if fasting glycemia < 140 mg%  FDG injection;

-if fasting glycemia > 200 mg/dl:  exclude patient

-if > 140 mg/dl et < 200 mg/dl  administration of IV Insuline and monitor glycemia until under 140 mg%.

Image acquisition

- start imaging at 60 minutes (+/- 5 minutes) post FDG administration
- whole body post-injection transmission scan or, CT (in case of PET-CT camera) for attenuation correction
- note body weight / length / glycemia

Image analysis

- visual analysis: 3 points score: normal, equivocal, pathological
- response analysis (always in relation to the baseline, pre-treatment, PET-imaging): 4 points score according to the criteria defined by the EORTC PET study group for assessing response using FDG18
  - Progressive metabolic disease
    - Increase in SUV of more than 25%
    - Visual increase in lesion extent (>20% in longest dimension)
    - New metastatic lesions
  - Stable metabolic disease
    - Increase in SUV < 25%, decrease < 15%
    - No visible increase in the extent of FDG uptake
  - Partial metabolic response
    - Reduction in SUV between 15 and 25% after 1 cycle of treatment
    - Reduction in SUV > 25% after more than 1 cycle of treatment
  - Complete metabolic response
    - Complete resolution of FDG-uptake

